## Abstract

**Background:**

Pre-pregnancy obesity and excessive gestational weight gain (GWG) are established risk factors for adverse pregnancy, delivery and birth outcomes. Pregnancy is an ideal moment for nutritional interventions in order to establish healthier lifestyle behaviors in women at high risk of obstetric and neonatal complications.

**Methods:**

Electronic-Personalized Program for Obesity during Pregnancy to Improve Delivery (ePPOP-ID) is an open multicenter randomized controlled trial which will assess the efficacy of an e-health web-based platform offering a personalized lifestyle program to obese pregnant women in order to reduce the rate of labor procedures and delivery interventions in comparison to standard care. A total of 860 eligible pregnant women will be recruited in 18 centers in France between 12 and 22 weeks of gestation, randomized into the intervention or the control arm and followed until 10 weeks of postpartum.

The intervention is based on nutrition, eating behavior, physical activity, motivation and well-being advices in which personalization is central, as well as the use of a mobile/tablet application. Inputs includes data from the medical record of participants (medical history, anthropometric data), from the web platform (questionnaires on dietary habits, eating behavior, physical activity and motivation in both groups), and adherence to the program (time of connection for the intervention group only). Data are collected at inclusion, 32 weeks, delivery and 10 weeks postpartum. As primary outcome, we will use a composite endpoint score of obstetrical interventions during labor and delivery, defined as caesarean section and instrumental delivery (forceps and vacuum extractor). Secondary outcomes will consist of data routinely collected as part of usual antenatal and perinatal care, such as GWG, hypertension, preeclampsia, as well as fetal and neonatal outcomes including premature birth, gestational age at birth, birth weight, macrosomia, Apgar score, arterial umbilical cord pH, neonatal traumatism, hyperbilirubinemia, respiratory distress syndrome, transfer in neonatal intensive care unit, and neonatal adiposity. Post-natal outcomes will be duration of breastfeeding, maternal weight retention and child weight at postnatal visit.

**Discussion:**

The findings of the ePPOP-ID trial will help design e-health intervention program for obese women in pregnancy.

**Trial registration:**

ClinicalTrials.gov Identifier: NCT02924636 / October 5th 2016.

## Background

Obesity is a major public health threat and has been listed as the sixth most important risk factor contributing to the overall burden of disease worldwide. In 2016, the World Health Organization estimated that there were 1.9 billion individuals with a body mass index (BMI) > 25 kg/m^2^ including nearly 325 million obese women (BMI > 30 kg/m^2^) [1]. Obesity affects approximately 15% of French population, involves more frequently young women [2] and represents a significant and increasing problem encountered in obstetrics [3]. There are well documented risks associated with obesity in pregnancy including gestational diabetes mellitus (GDM), hypertensive disorders and preeclampsia, thromboembolic diseases, stillbirth but also difficulties during delivery such as caesarean section, instrumental extraction related to macrosomia and sources of neonatal trauma. Following delivery, obese women are more likely to suffer from post-partum hemorrhage and to have longer hospital stays than women with a normal BMI (18.5–24.9 kg/m^2^) [3]. The effects of obesity may extend beyond health in pregnancy, as increasing evidence suggests that children of obese mothers or of those with excessive gestational weight gain (GWG) may be at greater risk of obesity because of exposure to adverse metabolic influences in utero, or in the early postnatal period [4]. Excessive GWG also increases the risk of maternal and neonatal complications. Excessive GWG, especially if superimposed on pre-existing excess of weight, increases the risk of obstetric complications including gestational hypertension, GDM, preeclampsia, and caesarean delivery in mothers; and macrosomia and long-term obesity in offspring [4]. In addition, excessive GWG would worsen maternal obesity in a long-term fashion, as excessive GWG is a major determinant of postpartum weight retention [5, 6].

The Institute of Medicine (IOM) published GWG guidelines according to the pre-pregnancy BMI in order to improve maternal as well as fetal outcomes. For a BMI between 20 and 25 kg/m^2^, recommended GWG should be between 11 and 16 kg, whereas for a BMI over 30 kg/m^2^, the GWG should be between 5 and 9 kg, in order to decrease the risk of adverse pregnancy outcomes. These recommendations are based on observational studies suggesting more favorable outcomes with lower GWG [7]. However, the United Kingdom National Institute for Health and Clinical Excellence guidelines on dietary and physical activity interventions for weight management before, during and after pregnancy, concluded that more evidence of outcome improvements from interventional studies is required before these or similar guidelines for limitation of GWG would be adopted [8].

In a systematic review of nine randomized trials including 743 overweight and obese pregnant women, there was no significant effect of interventions designed to limit GWG on weight gain or on delivery of a large-for-gestational-age (LGA) infant [9] and another systematic review of four trials addressing dietary interventions to decrease GWG, reported a reduction in GWG among 537 obese pregnant women without any influence on birth weight [10].

A recent systematic review of interventions in overweight and obese pregnant women observed that overall interventions were associated with reduced GWG, but without evidence for any effect in birth weight or caesarean section rates; although the available studies were considered of poor to medium quality [11]. A meta-analysis of 10 trials on GWG in normal, overweight and obese pregnant women, concluded that dietary advices during pregnancy appear effective in decreasing GWG and long term postpartum weight retention, but evidence for benefits on infant and maternal health was limited [12]. A second systematic review on GWG suggested that physical activity may reduce GWG with little evidence for improved outcomes [13]. In a third systematic review of 12 trials in normal BMI and obese pregnant women (*n* = 1656 women), dietary and physical activity interventions were effective in reducing GWG, but there was considerable heterogeneity in outcomes [14]. The analysis highlighted differences in sample characteristics and aspects of intervention design, content, delivery and evaluation, which might explain discrepancies in effectiveness. The most recent meta-analysis included 44 trials and concluded that dietary and lifestyle interventions in pregnancy could reduce GWG and improve outcomes for both mothers and newborns, although the overall evidence level was low to very low for major outcomes such as preeclampsia, GDM, gestational hypertension, and preterm delivery. Only five trials could be used to evaluate the effect of interventions on caesarean section. The authors stated that ongoing effectiveness trials should focus on clinically relevant outcomes such as caesarean section and instrumental delivery [15]. The LIMIT trial indicated that provision of lifestyle advices to women who were overweight or obese during pregnancy did not reduce the risk of large for gestational age (LGA) infants or improve maternal outcomes in pregnancy and birth, but was associated with a significant reduction in risk of macrosomia defined as birthweight superior to 4 kg [16].

In total, the current available data suggest that dietary and physical interventions in pregnancy are effective at reducing the GWG compared to usual care, while they do not increase the risk for small-for-gestational-age (SGA) or low birth weight in newborns.

However, controlling GWG within the recommendations is not easily achievable for many pregnant women, especially those already overweight or obese. Indeed, 30 to 50% of obese women have a GWG beyond the guidelines, even in the groups who follow an antenatal lifestyle program [15]. Although the current IOM guidelines recognize that “interventions will be needed to assist women, particularly those who are in overweight or obese at the time of conception” to meet these recommendations. There is little high-quality evidence available from randomized trials to determine the best approach to manage GWG in pregnancy. Published studies were mainly monocentric with interventions judged to be too complex or too expensive to be implemented widely. There was considerable variation in the nature of the interventions provided in the previously published works, ranging from single session with a dietician to dietetic counselling sessions at each antenatal visit. Although the provision of a more intensive program has been associated with greater weight loss in non-pregnant individuals [17, 18], the ability to provide this type of intervention at a broader antenatal population remains questionable. Moreover, there are barriers to lifestyle modification in pregnant women, including lack of time and energy, competing work and family demands, and lack of childcare [19].

Considering implementation of the web in the society, we hypothesized that using a personalized and pragmatic program combining nutritional, physical activity, motivational and well-being counselling, would address this issue. A pilot study using SMS messaging intervention demonstrated the feasibility, acceptability, and potential efficacy of low-intensity and expendable intervention to help overweight and obese women reduce GWG. Although the results did not reach statistical significance due to small sample size (*n* = 14 in the intervention group and *n* = 9 in the control group), women in the intervention group had a GWG of six pounds less than participants in the control group (95% CI − 15.9, 4.0; *p* = 0.24) at 40 weeks of gestation [20].

The introduction of the new digital technologies in the society increased since the last century. For people, Internet technologies have become so ubiquitous as to seem invisible. The implementation difference of the Internet is low between workers and managers [21], and mobile phone use appears to be similar across all socioeconomic groups [22]. In fact, some socially disadvantaged populations are *more* likely to send messages everyday than their more advantaged counterparts. Providing a personalized prevention program is innovative by the use of technologies that are essential tools for daily life: cell phones, computers or tablets to access the Internet and emails. Thus, the use of tools that become universal could help to sensitize the pregnant women. Moreover, pregnancy is a very privileged time to implement good health habits and to diffuse them within the family. E-mail and newsletter interventions, as well as online forum should be more acceptable for obese pregnant than face-to-face and telephone counselling or group sessions. Women will not feel judged or devalued. An electronic intervention may be especially useful for self-monitoring because of the potential for providing both support and immediate feedback based on a patient’s specific goals. This system will fight against geographical or social disparities. Indeed, the Internet is spread to the entire country regardless of health resources available nearby. The “Institut National de Statistiques” considers that only 3% of the French citizens do not have the possibility to access to the Internet [23]. Online interventions have emerged as a popular strategy to promote healthy behaviors. However, the limited amount of work done with Internet-based obesity interventions has provided little in the way of solid and reproducible results. A systematic review of eight Internet-based randomized trials reported some improvement with mixed findings, due to small sample sizes. The authors stated that the research including the use of technologically based interventions should be amplified and targeted to answer specific questions [24].

To our knowledge, there is no published work that studied the effect of a technologically based intervention during the pregnancy. A program was recently tested in the post-partum period. The Diabetes Prevention Program demonstrated that an intensive, face-to-face lifestyle intervention could achieve weight loss and reduce incidence of type 2 diabetes in middle-aged adults at high-risk, including women with a GDM history [25]. However, because face-to-face lifestyle intervention studies in post-partum women have had limited success [25, 26] and given the multiple barriers to face-to-face interventions, and the widespread use of the Internet, the authors adapted the Diabetes Prevention Program into a web-based lifestyle intervention using web-based technology to deliver lifestyle interventions for women with recent GDM. The study demonstrated the feasibility and efficacy of the web-based lifestyle modification program to decrease postpartum weight retention in the first postpartum year for women with recent GDM. The authors concluded that this program is at low cost to implement and has potential for broad dissemination [19]. These data suggest that a web-based program should be tested in obese pregnant women to limit GWG.

The purpose of our study is to assess the efficacy of an e-personalized program including antenatal dietary and lifestyle advices in pregnancy to reduce the rate of labor procedures and interventions in comparison to standard care. As secondary objectives, we will investigate whether the e- program may improve the health of the mothers and their newborns, compared to a control group allocated to standard care. Maternal secondary outcomes include reducing GWG, increasing the proportion of participants having a GWG within the guidelines, reducing the risk of hypertension, preeclampsia, and GDM, reducing fat and sugar intake, increasing physical activity, increasing breastfeeding and duration, reducing weight retention after childbirth. For newborns, secondary outcomes will consist of improving birth weight, reducing risk of macrosomia, trauma associated with childbirth and low Apgar score, reducing the use of phototherapy for hyperbilirubinemia, as well as reducing number of admissions to neonatal intensive care unit and number of infants with excessive weight at postnatal visit.

## Methods

### Study setting

ePPOP-ID is an open multicenter randomized controlled trial, which involves 18 university and/or regional hospitals from nine regions in France (study design illustrated in Fig. 1 and Table 1). These centers deliver approximately 30,000 patients per year, which leads to a potential of 2400 to 3000 obese pregnant women per year (i.e. 8 to 10% of the pregnant women being obese), which makes 200 to 250 eligible women per month.

**Fig. 1 Fig1:**
[figure not shown]
Protocol overview. Electronic-Personalized Program for Obesity during Pregnancy to Improve Delivery (ePPOP-ID) is an open multicenter randomized controlled trial which will assess the efficacy of an e-health web-based platform offering a personalized lifestyle program to obese pregnant women in order to reduce the rate of labor procedures and delivery interventions in comparison to standard care. A total of 860 eligible pregnant women will be recruited in 18 centers in France between 12 and 22 weeks of gestation, randomized into the intervention or the control arm and followed until 10 weeks of postpartum. For both arms, inputs include data from the medical record of participants and the web platform (online questionnaires), collected at inclusion, 32 weeks, delivery and 10 weeks postpartum

**Table 1 Tab1:**
[figure not shown]
Schedule of enrolment, interventions, and assessments for ePPOP-ID Study

### Recruitment and eligibility criteria

Screening of participants is performed by midwives and obstetricians of involving hospitals at the first prenatal visit, between 12 and 14 weeks of gestation, at which a verification of inclusion and exclusion criteria is anticipated for the inclusion visit.

To optimize the recruitment, the study was presented to all caregivers that perform visits. Flyers and posters are placed in the waiting rooms of the prenatal consultation area in order to inform potential participants.

Inclusion visit takes place between 12 and 22 weeks. Pregnant women with a singleton pregnancy, a pre-pregnancy BMI between 30 and 40 kg/m^2^, and aged of 18–45 years-old are included. Other eligibility criteria consist of providing written informed consent, having access to internet (by using phone, tablet or computer), being comfortable with the use of internet, and having an email address. Exclusion criteria consist of having a history of more than 2 miscarriages, severe heart disease (arrhythmias, history of myocardial infarction), unstable thyroid disease, uncontrolled hypertension, pre-gestational diabetes, bariatric surgery or any medical condition that may interfere with physical activity during pregnancy, no health insurance, or being legally assisted or unable to consent. Participants can not follow other lifestyle interventions during their participation in the ePPOP-ID trial. The total duration of the trial will be 50 months with an enrolment period of 24 months. The participants are withdrawn of the study if they lose the ability to connect to the program.

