### Randomization

The randomization procedure is performed at the end of the inclusion visit, centralized and stratified by center. The 1:1 assignment sequence (based on blocks of four and the use of a computer random-number generator) is produced by the sponsor. The randomization list is not disclosed to the study centers, monitors, statisticians or to the trial team. After collection of the email address of participants, an invitation is sent to each participant to connect to the web-based platform, in order to complete the registration procedure (i.e. to complete the profile and define a login password), as well as fill in the online initial assessments. The intervention group also has access to the personalized electronic lifestyle program whereas the control group not. Due to the nature of the intervention a blind study was not achievable.

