### Data collection

#### Clinical variables

At inclusion visit between 12 and 22 weeks, demography, medical and family history and current pregnancy health information are collected. Anthropometric variables (weight and height) are measured; blood and urine samples are drawn. No additional follow-up visit is required, as women benefit of the usual care for pregnancy (according to the French guidelines) which consists of 7 prenatal visits and 1 post-natal visit between 6 and 10 weeks after delivery. Information is collected from maternal medical records regarding health during pregnancy including gestational hypertension, preeclampsia and GDM. All women in both groups undergo a 75 g-oral glucose tolerance test (75 g glucose oral load after a fasting period of 10 h minimum) between 24 and 28 weeks. The diagnosis of GDM is made according to the IADPSG criteria (i.e. fasting plasma glucose ≥5.1 mmol/L [0.92 g/L] and/or 1-h glucose ≥10 mmol/L [1.80 g/L] and/or 2-h glucose ≥8.5 mmol/L [1.53 g/L]). The beginning of labor and the delivery mode are collected as well as the occurrence of post-partum hemorrhage. Neonatal and postnatal outcomes include the occurrence of traumatism due to childbirth, Apgar score, umbilical cord pH, admission to neonatal unit and use of phototherapy for hyperbilirubinemia. To address the influence of the intervention on neonatal growth and adiposity, neonatal anthropometric variables (weight, length, adiposity skinfolds) are measured within the first 24 h. At the post-natal visit, maternal demographic data, health since the delivery (post-partum complications such as fever, hemorrhage, thromboembolic events) and duration of breastfeeding are obtained. Maternal anthropometric variables (weight, height) are measured. To address the safety and the impact of the intervention on child health, details regarding the health since birth is also obtained. To address the influence of the intervention on infant adiposity, infant length and weight are measured at birth.

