### Statistics

Statistical analyses will be independently performed by the Biostatistics Department of University of Lille. Data will be analyzed using the SAS software (SAS Institute Inc., Cary, NC, USA) and all statistical tests will be performed with a 2-tailed alpha risk of 0.05. A detailed statistical analysis plan will be written and finalized prior to the database lock. For each exploratory analysis, a statistical analysis plans will be provided before any data analysis. Baseline characteristics will be described for each group. Quantitative variables will be expressed as mean (± standard deviation), median (± interquartile range) and 95% confident interval. Qualitative variables will be expressed as frequencies and percentages. Normality of distribution will be assessed graphically and using the Shapiro-Wilk test. The primary analysis for primary and secondary endpoints will be conducted on the intention-to-treat principle. A secondary per-protocol analysis will be performed.

The primary endpoint (rate of delivery interventions) will be compared between the two groups using the Chi-square test. Absolute and relative risk difference (intervention vs. control) and their 95% confidence intervals will be calculated. For the secondary objectives, binary endpoints will be compared between the two groups using chi-square tests or Fisher’s exact tests when the expected cell frequency will be inferior to 5. Quantitative endpoints will be compared between the two groups using student *t* tests or Mann-Whitney U tests in case of non-normal distribution (except if a log-transformation can be applied to normalize the data). For quantitative endpoints involving repeated measures, a linear mixed model will be used. This model allows to perform an ANOVA for repeated measures taking into account the correlation between the repeated measures. The choice of the covariance in the models will be based on the AIC criteria and normality of residuals will be checked.

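### Women who can no longer connect to the program are withdrawn from the whole study after randomization, which conflicts with the intention-to-treat primary analysis unless their outcomes are still collected

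*Protocol article*

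**What the plan says.** The rule is the last sentence of Recruitment and eligibility criteria: "The participants are withdrawn of the study if they lose the ability to connect to the program". It names the study as what the woman leaves, and the program as what she can no longer reach.

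The Randomization section gives the timing and who has what:

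- "The randomization procedure is performed at the end of the inclusion visit, centralized and stratified by center".
- In both arms, "an invitation is sent to each participant to connect to the web-based platform", for registration and the initial questionnaires.
- "The intervention group also has access to the personalized electronic lifestyle program whereas the control group not".

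The Statistics section states: "The primary analysis for primary and secondary endpoints will be conducted on the intention-to-treat principle". It then adds: "A secondary per-protocol analysis will be performed".

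Under Clinical variables, the component of the primary endpoint is recorded as ordinary clinical data: "The beginning of labor and the delivery mode are collected as well as the occurrence of post-partum hemorrhage". The same section says that follow-up is usual pregnancy care with no extra trial visits.

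**The concern.** Intention to treat needs the outcome of every randomized woman, counted in the arm she was assigned to. A rule that takes women out of the study because they can no longer use the intervention puts a per-protocol criterion into trial conduct, ahead of any analysis. If sites follow it in the ordinary sense and stop collecting data, the analysis plan cannot restore the missing delivery outcomes.

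The loss would also be avoidable. Only the online questionnaires need a connection; the mode of delivery does not. If the rule acts in one arm, and the women it removes differ in risk from the rest, the randomized comparison on the primary endpoint is distorted in a direction that nobody can know beforehand.

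**Working it through.** **1. Is the event after randomization?** Internet access is an entry criterion, so losing it is a later event. Randomization closes the inclusion visit. The platform invitation follows, and the program starts only once the initial questionnaires are complete (Participant timeline). The rule therefore acts after randomization.

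**2. Which arm does it reach?** The Randomization section separates the platform (both arms) from the program (intervention arm). The Intervention section likewise describes a program hosted on a platform. Read literally, a control woman cannot lose a connection to something she was never given. If program is used loosely for platform, controls can be withdrawn as well. Removal is still after randomization, but less one-sided.

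**3. Is the outcome still obtainable?** Yes. Delivery mode is a clinical variable obtained under usual care. The article does not say that it is still collected after this withdrawal.

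**4. The plan's own figures.** Inputs from Sample size: 50% against 40%, two-sided alpha 5%, power 80%. With pooled variance and no continuity correction,

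n = [1.960·√(2·0.45·0.55) + 0.842·√(0.50·0.50 + 0.40·0.60)]² / 0.10² = 387.3 per arm.

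This rounds up to 388; the article states 387, at which power is 79.97%. Dropout inflation gives 774/(1 − 0.10) = 860, as stated. These figures are not in dispute. They fix 430 randomized per arm.

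**5. Size of a possible bias.** The documents give no withdrawal rate under this rule and no risk for the women concerned, so both are assumptions. Take no true effect, 50% risk in both arms, and a share d of the intervention arm withdrawn and left out, with risk r. Then:

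- observed intervention rate: p = (0.50 − d·r)/(1 − d)
- spurious difference: p − 0.50
- type I error: normal-approximation rejection probability of the two-sided pooled test, with 430 controls and 430·(1 − d) intervention women.

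Example, d = 10% and r = 70%: p = (0.50 − 0.07)/0.90 = 0.478, a shift of −2.2 points. The standard error with 430 and 387 women is 0.035, and the rejection probability is 9.7%.

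| Share withdrawn, d | Shift at r = 60% | Type I error | Shift at r = 70% | Type I error |
|---|---|---|---|---|
| 1% | −0.1 points | 5.0% | −0.2 points | 5.0% |
| 3% | −0.3 | 5.1% | −0.6 | 5.4% |
| 5% | −0.5 | 5.3% | −1.1 | 6.1% |
| 10% | −1.1 | 6.2% | −2.2 | 9.7% |

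At r = 50% the shift is zero and the type I error stays at 5.0% for every d. At r = 40% or 30% the shifts have the same size with the opposite sign. The planned effect, for scale, is 10 points.

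**The case against.** The strongest reply is that the eligibility section governs participation and the Statistics section governs analysis. The article never says that withdrawn women leave the primary analysis, and handling of withdrawals is commonly left to the full protocol or analysis plan. A reader might infer that the rule makes an intention-to-treat analysis impossible. The text does not support that: intention to treat survives if delivery mode is still taken from the record and analysed by assigned arm. What remains is that the article states an explicit rule of withdrawal from the study, with nothing to say that collection continues, and an analysis plan cannot recover data that sites did not collect.

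Three further objections limit the point.

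- **One arm.** The rule speaks of participants generally and stands among criteria that apply to everyone. The one-arm reading is the more literal, but it is not certain.
- **Trigger.** It is inability to connect, not low use. Under Enhancing adherence and compliance, absence of connection is met with reminders. Reading the rule as removing poorly engaged women would be wrong.
- **Size.** The Background cites only 3% of French citizens without possible internet access, and this trial enrols women who already have it. That favours the low rows of the table, although the 3% is a population figure and not a rate of losing access during the trial. The 60–70% risk is assumed too. A reader might also infer that the rule consumes the 10% allowance for drop-outs and missing data; with no withdrawal rate given, that cannot be shown.

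None of these objections removes the conflict between the two statements or the case for the correction.

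**Conclusion.** The sentence is wrong as written and should be fixed. It withdraws randomized women from the study on a post-randomization event, in one arm on the literal reading, while the primary analysis is declared intention-to-treat and the primary outcome remains available without a connection.

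The consequence is uncertain in size and sign. Under the stated assumptions it runs from negligible (about 0.1–0.6 points when 1–3% of the intervention arm is removed) to modest (0.5–2.2 points at 5–10%), and it is nil if withdrawn women carry average risk. A substantial inflation of the type I error might be inferred from the upper end of the table, but the documents contain nothing that makes that end likely. The reason to act is that the correction is simple and uncollected outcomes may be hard to recover later.

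**What to change.** Replace the sentence with wording to this effect: *Loss of connection ends use of the platform only. The woman remains in the trial; delivery mode and neonatal and postnatal data are collected from the maternity record unless she withdraws consent; and she is analysed in the arm to which she was assigned.*

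Add a matching instruction to the electronic case report form, so that sites record the end of platform use separately from the end of follow-up. If any women have already been withdrawn under this rule, recover their delivery outcomes as far as their consent allows.

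The cost is a one-sentence amendment and one form instruction. No visits are added, because these outcomes arise in routine care, and the sample size does not change.
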